## Abstract

**Background:**

Postherpetic neuralgia (PHN) is the most common complication attributed to herpes zoster, which involves the reactivation of residual varicella zoster virus. It has been reported previously that pre-emptive amitriptyline following acute herpes zoster has shown latent positive effects in the prevention of PHN. In this study, by interfering with the same targets, norepinephrine and serotonin, we aim to evaluate whether pre-emptive duloxetine may proactively prevent PHN development.

**Methods:**

This is a nationwide multicentric, randomized, open-label, blinded-endpoint study that will recruit 750 participants from 18 primary centres in China. Patients aged more than 50 years who are diagnosed with uncomplicated HZ, present with vesicles within 72 h of their emergence, and have an average pain score of at least 40/100 mm on a visual analogue scale (VAS, 0 mm = no pain, 100 mm = worst possible pain, at opposite ends of a 100-mm line) will be recruited for this study. Participants will be randomized into a duloxetine arm and a control arm. Participants allocated to the duloxetine arm will be given antivirals, analgesics and duloxetine, while those allocated to the control arm will receive antivirals and analgesics but no duloxetine. The primary outcome of this study is preventive efficacy against PHN, which will be evaluated based on a 100 mm VAS. Any pain scores other than 0 mm on the VAS 12 weeks after HZ onset will be defined as PHN. The secondary outcomes will consist of the average weekly VAS score, the average weekly consumption of each analgesic, weekly feature of the pain, patients’ quality of life based on the 12-item Short-Form Health Survey, Patient Global Impression of Change Scale, sleep quality as evaluated by the Pittsburgh Sleep Quality Index and adverse events during the study period.

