### Strategies to improve adherence to interventions {11c}

Once assigned to one of the two study groups, a pharmacological protocol will be given as per allocation. Physicians and research assistants will be responsible for instructing participants to follow the protocols correctly, and to ensure adherence to interventions. After recruitment, each participant will be given a pain diary (PD), in which all outcomes can be recorded by the participants themselves during the study period. The specific recording criteria are as follows: (i) the VAS score will be recorded every morning before breakfast, (ii) AEs and consumption of each analgesic will be recorded every evening before bed, and (iii) the 12-item Short-Form Health Survey (SF-12), Patient Global Impression of Change Scale (PGIC) and Sleep quality as measured by the Pittsburgh Sleep Quality Index (PSQI) will be self-assessed at baseline and upon completion of weeks 4, 8, and 12. During the study period, the research assistants will monitor the participants’ completion of the PDs and deliver reminders as necessary through telephone calls or social media. At the end of week 12, the PDs will be collected by the research assistants and stored by the Data Safety Monitoring Board (DSMB). The research assistants will be available 24 h a day, 7 days a week, to answer any questions related to the study.

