### Relevant concomitant care permitted or prohibited during the trial {11d}

For all participants, 1000 mg valacyclovir will be administered three times a day for 7 days, and analgesics will be given according to the three-step World Health Organization (WHO) pain ladder [27]. Non-opioids will be preferred for mild pain, weak opioids plus non-opioid analgesics will be recommended if moderate pain is developed, and strong opioids plus non-opioids will be provided for severe pain. All selected analgesics will be administered until *VAS* ***=*** *0*. Once VAS = 0, analgesics will be discontinued. Treatments not mentioned in this protocol will not be allowed unless approved and standardized by the research team. All unmentioned treatments will be recorded thoroughly by the research assistants.

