### Sample size {14}

Based on the reported prevalence, the incidence of PHN in China is approximately 30% [2] after VZV reactivation. We predict that the same incidence will be observed in participants from the control arm. For participants in the duloxetine arm, the preventive protocol is expected to reduce the incidence to 20%. Assuming a 15% rate of loss to follow-up, a total of 750 participants would provide 90% power to detect the significant difference in the incidence of PHN using a 2-tailed alpha of 0.05.

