### Statistical methods

#### Statistical methods for primary and secondary outcomes {20a}

Statistical analyses will be performed using the SPSS 25.0 software package for Windows (SPSS, Inc., Chicago, IL, USA). The baseline and outcomes for the intervention will be compared to the control arm for primary analysis. Continuous variables will be expressed as the mean (SD) or median (IQR) and compared using Student’s *t* test or the Mann-Whitney *U* test. Normality will be tested using the Kolmogorov-Smirnov test. Categorical variables will be expressed as the number of patients (percentage) and compared using the chi-squared test or Fisher’s exact test. A 2-tailed alpha of 0.05 will be used as the threshold of statistical significance. The incidence of PHN in each arm at the end of week 12 will be compared using the chi-squared test. Subgroup analyses will be performed for age, gender, time to medication, maximum duloxetine dosage and average weekly pain score. Multiple logistic regression will be used to evaluate and determine the interference of the above confounding factors in the primary outcome. All analyses will be performed using both the intention-to-treat and per-protocol principles, and the final conclusion will be determined in line with the intention-to-treat principle.

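### Weak-opioid consumption compared on its own has no clear direction, because the analgesic ladder replaces the weak opioid when pain becomes severe

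*Protocol article*

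**What the plan says.** The abstract of the protocol article names "the average weekly consumption of each analgesic" among the secondary outcomes, and the list under Outcomes {12} repeats the per-drug form. Neither place mentions a total, a class-level measure or a conversion to a common scale.

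The data come from the pain diary: "AEs and consumption of each analgesic will be recorded every evening before bed" (section {11c}, repeated in {18a}).

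Section {11d} on concomitant care ties the type of drug to the severity of pain. "Non-opioids will be preferred for mild pain"; then "weak opioids plus non-opioid analgesics will be recommended if moderate pain is developed, and strong opioids plus non-opioids will be provided for severe pain". At the lower end, "Once VAS = 0, analgesics will be discontinued".

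Section {20a} gives one general rule for the analysis: "Continuous variables will be expressed as the mean (SD) or median (IQR) and compared using" a t test or a Mann-Whitney test, at a two-sided 0.05. No separate method is given for analgesic use.

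**The concern.** The natural question behind this outcome is whether participants on duloxetine need less analgesia. A measure that answers it should fall when pain improves and rise when pain worsens. Weak-opioid consumption does not behave that way under this ladder. It is absent at the mild step, present at the moderate step and, as the rule is written, absent again at the severe step. The same fall can come from participants who got better or from participants who got worse.

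At stake is the reading of one secondary outcome. A between-arm difference in weak-opioid use, or the lack of one, could be taken as evidence about duloxetine when it carries no clear direction. The primary outcome, any pain above zero on the VAS at 12 weeks, does not use these data.

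**Working it through.** The article states no figure for analgesic consumption, so there is no plan figure to reproduce. The check sets the outcome against the ladder and then illustrates it with assumed shares.

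**Step 1. Which class is present at each step (section {11d}).**

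| Pain | Non-opioid | Weak opioid | Strong opioid |
|---|---|---|---|
| VAS 0 | no | no | no |
| Mild | yes | no | no |
| Moderate | yes | yes | no |
| Severe | yes | no | yes |

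Only the weak-opioid column goes from no to yes and back to no as pain rises. The non-opioid column stays at yes once there is pain, and the strong-opioid column is yes only at the top. For those two classes, moving up the ladder never lowers use.

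**Step 2. Illustration.** Assumptions: one unit per drug per week, and shares of an arm at VAS 0, mild, moderate and severe as listed. None of these shares is in the article. Mean use per participant is then:

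- non-opioid = mild + moderate + severe
- weak opioid = moderate
- strong opioid = severe

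| Row | VAS 0 / mild / moderate / severe | Non-opioid | Weak | Strong |
|---|---|---|---|---|
| A, reference | 0.10 / 0.25 / 0.50 / 0.15 | 0.90 | 0.50 | 0.15 |
| B, 15% go from moderate to severe | 0.10 / 0.25 / 0.35 / 0.30 | 0.90 | 0.35 | 0.30 |
| C, 15% go from moderate to mild | 0.10 / 0.40 / 0.35 / 0.15 | 0.90 | 0.35 | 0.15 |

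B is worse than A and C is better than A, yet weak-opioid use falls by 0.50 − 0.35 = 0.15 in both. Comparing B with C directly, weak-opioid use is equal at 0.35 although C has clearly less pain.

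A larger shift behaves the same way. From 0.10 / 0.40 / 0.40 / 0.10 to 0.10 / 0.40 / 0.10 / 0.40, which is worse pain, weak-opioid use falls from 0.40 to 0.10, strong-opioid use rises from 0.10 to 0.40, and non-opioid use stays at 0.90.

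**Step 3. Net sign between arms.** Suppose duloxetine keeps a share *b* at moderate pain that would otherwise reach severe, and moves a share *a* from moderate to mild. Then

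weak-opioid use, duloxetine minus control = *b* − *a*.

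Both movements are benefits, but they enter with opposite signs. The difference is positive, zero or negative according to which is larger, and the article gives neither.

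**Step 4. Does a common opioid scale restore a direction?** Let a week on the weak opioid count *w* and a week on the strong opioid count *s* in morphine equivalents. Mean opioid use is *w* × moderate + *s* × severe. Moving a share *d* from moderate to severe changes it by *d*(*s* − *w*), which is positive when *s* exceeds *w*. Moving *d* from moderate to mild changes it by −*dw*, which is negative. The measure then follows pain, on the assumption that a week on the strong opioid carries more equivalents than a week on the weak one.

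Two simpler summaries would not do as the lead. The share using any opioid is 0.50 + 0.15 = 0.65 in A and 0.35 + 0.30 = 0.65 in B. Any-analgesic use is 0.90 in all three rows.

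**The case against.** The strongest reply is that the planned outputs already expose the problem. Every analgesic is reported, and average weekly VAS is a secondary outcome too. If an arm did worse, a reader would see less weak opioid beside more strong opioid and a higher VAS. That is fair: the misreading needs the weak-opioid row to be taken alone, and this limits how much the point matters. But no combined comparison is stated, so the synthesis is left to the reader.

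A second reply is that conversion tables, handling of zeros and derived summaries belong in the analysis plan, which is not shown. That holds for the details. The per-drug form, however, is what the abstract and the outcome list themselves fix.

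A reader might infer four stronger things, and the document supports none of them:

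- **That lower use of any one drug can signal worse pain.** Under the ladder this holds only for weak opioids.
- **That the weak-opioid comparison would favour the control arm if duloxetine works.** Step 3 of the working shows that the net sign depends on flows in both directions that are not stated.
- **That the outcome produces a large, countable number of tests.** The article does not say how many analgesics are used or that each is tested in each week.
- **That product choice is uncontrolled across the 18 centres.** This is a condensed article. It refers to an operation manual, and it bars treatments it does not mention unless the research team approves and standardises them. Silence on products here does not show that none is specified elsewhere.

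**Conclusion.** The point holds in a narrow form. Because the outcome is fixed drug by drug and the ladder puts a strong opioid in place of the weak one for severe pain, a between-arm comparison of weak-opioid consumption has no clear direction. Non-opioid and strong-opioid consumption do not share this defect.

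The conclusion rests on reading the severe-pain step as written, with strong opioids and non-opioids and no weak opioid. Its size in this trial cannot be stated, because no distribution over the ladder steps is given. The 0.15-unit fall, identical for improvement and worsening, shows only that the ambiguity can be complete. One secondary outcome is affected and the primary outcome is not, so this is a cheap improvement rather than a serious fault.

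**What to change.** Define the analgesic outcome as one lead summary per participant over follow-up, derived from the existing diary. One example is total opioid dose in oral morphine equivalents by a conversion table fixed in advance, with a value of zero for participants who use none. Support it with days on any analgesic and the highest ladder step reached. Keep consumption of each drug as a descriptive table without a between-arm test.

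The cost is the conversion table and a few lines of wording in the outcome definition and analysis plan. Treatment, visits and data collection do not change, provided that the diary entries identify the product and dose. The downside is that non-opioids have no place on the opioid scale and can be reported only as days of use, so the lead measure speaks to opioid need rather than to all analgesia.

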**Discussion:**

This study will investigate a prophylactic approach for reducing the prevalence of postherpetic neuralgia with duloxetine and will add significant new knowledge on the preventive effects of duloxetine on PHN.

**Trial registration:**

Clinicaltrials.gov NCT04313335. Registered on 18 March 2020.

## Administrative information

Note: the numbers in curly brackets in this protocol refer to SPIRIT checklist item numbers. The order of the items has been modified to group similar items (see http://www.equator-network.org/reporting-guidelines/spirit-2013-statement-defining-standard-protocol-items-for-clinical-trials/).

## Introduction

### Background and rationale {6a}

Postherpetic neuralgia (PHN) is the most common complication attributed to herpes zoster (HZ), which involves the reactivation of residual varicella zoster virus (VZV). Although the definition varies, pain that persists for 4 weeks to 6 months following acute HZ onset is recognized as PHN. Risk factors [1] for the development of PHN include older age, skin damage and pain intensity during acute HZ. In China, the prevalence of HZ is reported to be 7.7% [2] among the adult population, and an estimated 2.77 [3] million cases are diagnosed annually. Among those cases, 30% [2] are predicted to develop PHN after 12 weeks. Recent investigation [4] has shown that PHN is associated with sleep disturbances, lower quality of life, restricted daily activities and increased medical costs, all of which impose heavy burden on the patient and their finances. In addition, neuropathic pain [5] often persists for months or years and is refractory to drugs. Although a group of medications such as antidepressants, antiepileptics and topical agents are recommended by international guidelines, management of PHN is still challenging. Current therapeutic modalities fail to meet clinical expectations, as significant pain relief is achieved in less than 50% of patients [6] even with the most effective medications for PHN. Preventive and pre-emptive management [7] has been advocated for PHN in the future.

As to PHN prevention, HZ vaccination has been commonly administered [8] in the aged population. The efficacy of this treatment has been indicated and well-conducted [9–11]. When administered prior to VZV reactivation, the HZ vaccine significantly reduces the incidence of HZ and PHN in the following years. Treatment for acute HZ is believed [12] to reduce the incidence of PHN by interfering with virus duplication, the inflammatory response and peripheral or central nociceptor activity. Antivirals [13] are recommended for acute HZ in certain non-immunocompromised patients, which are believed to repress viral replication. Simultaneously, the process of lesion healing is accelerated, and new lesion formation is reduced. Based on a systematic review, pain during acute HZ onset is alleviated by the administration of antivirals, while PHN remains [14]. Corticosteroid therapy [13], although controversial, is an alternative adjuvant to antivirals in acute HZ. Studies [15, 16] have shown that corticosteroids are related to early healing, improved daily activity and reduced pain intensity. However, another systematic review has shown that corticosteroids have a limited ability to decrease the incidence of PHN. The voltage-gated calcium channel blocker gabapentin is recommended as the first-line medication [7] for PHN and has been extensively applied in clinical practice. In a recent retrospective study [17], premedication with gabapentin administered for other peripheral neuropathies, including neuropathy caused by diabetes, adverse drug effects, radiotherapy and other diseases, before acute HZ onset was found to assist in the prevention of PHN. A similar outcome was observed in an uncontrolled open-label study [18]. The incidence of PHN was decreased after combination treatment with gabapentin and valacyclovir in patients with acute HZ. In contrast, Bulilete et al. [19] found no evidence that 1 week of valacyclovir (1000 mg tid) plus 5 weeks of gabapentin (titrated from 300 to 1800 mg per day) beginning within 3 days after HZ onset helped prevent PHN. Lee et al. [20] found that 12 weeks of gabapentin (900 mg per day) beginning within 4 days after HZ onset failed to reduce the incidence of PHN. Amitriptyline is a tricyclic antidepressant (TCA) that increases the availability of both norepinephrine and serotonin. A previous randomized study [21], in which amitriptyline administration was combined with antivirals for 90 days after acute HZ diagnosis, showed that the combined treatment did not achieve a significant preventive effect on PHN at 3 months after HZ onset compared to placebo. However, a delayed reduction in PHN incidence was found for amitriptyline at 6 months after HZ onset. In summary, beyond the vaccine, there is little evidence of a method to reduce the incidence of PHN after VZV reactivation. Therefore, convincing preventive approaches that begin after VZV reactivation are needed for researchers and clinicians.

Existing evidence [22] suggests that the transformation of HZ to PHN involves neural sensitization. Abnormal functional and structural changes have been observed in PHN brains and reported in recent studies [22]. These changes are believed to be closely related to the chronification of PHN. Descending inhibitory serotonergic and noradrenergic pathways [23] regulate the neural excitability of the dorsal horn. The inhibitory balance shifts in the context of neuropathic pain. Duloxetine has been approved for the treatment of neuropathic pain and recommended as the first-line [24] pharmacotherapy. The mechanism of action of duloxetine regarding the inhibition of serotonin and norepinephrine reuptake may enforce or reinforce the inhibitory mechanism, maintain or reconstruct inhibitory balance and potentiate pain alleviation or the avoidance of persistent pain induction.

In a previous study, pre-emptive amitriptyline has shown latent preventive effects on PHN by interfering with central reuptake of norepinephrine and serotonin, although there was no statistical difference in the reduction of incidence of PHN until 6 months after VZV reactivation. The limited sample size and unstandardized antiviral therapy seemed to have had an impact on the preventive efficacy. Consequently, we speculate that pre-emptive duloxetine, which has similar mechanisms and is safer in older patients [25], provided shortly after VZV reactivation may proactively stabilize the inhibitory balance before sensitization occurs. If successful, this stabilization will help reduce the incidence of PHN. We hypothesized that positive outcomes will be concluded upon enlarged sample size and standardized antiviral therapy. Thus, this multicentric, randomized, open-label, blinded-endpoint study was designed to evaluate whether premedication with duloxetine within 72 h after VZV reactivation has a promising preventive effect on PHN.

### Objectives {7}

The aim of this study is to evaluate whether premedication with duloxetine within 72 h after VZV reactivation has a promising preventive effect on PHN.

### Trial design {8}

This PROCESS trial is a multicentric, randomized, open-label, blinded-endpoint study, designed to evaluate whether premedication with duloxetine within 72 h after VZV reactivation has a promising preventive effect on PHN. In total, 750 participants will be recruited from 18 different hospitals all over China. Participants will be assigned to either the duloxetine arm or the control arm in an allocation ratio of 1:1. The timeline and detailed schedule of the study are illustrated and summarized in Fig. 1.

**Fig. 1 Fig1:**
[figure not shown]
The timeline and detailed schedule of the PROCESS trial

## Methods: participants, interventions and outcomes

### Study setting {9}

We designed a nationwide multicentric, randomized, open-label, blinded- endpoint study that will recruit at least 750 participants from Beijing Tiantan Hospital, China-Japan Friendship Hospital, The Second Hospital of Tianjin Medical University, Taiyuan Central Hospital of Shanxi Medical University, Linfen Fourth People’s Hospital, Shandong Provincial Hospital, Qingdao Municipal Hospital (Group), Huai’an Second People’s Hospital, The First Hospital of China Medical University, The Second Affiliated Hospital of Zhengzhou University, Fujian Provincial Hospital, Cangzhou Central Hospital, The People’s Hospital of Fujian Province, Beijing Tsinghua Chang Gung Hospital, Peking University International Hospital, Tianjin First Central Hospital, Tianjin Huanhu Hospital and Baoding First Central Hospital in 10 provinces and cities in China. We plan to begin trial recruitment on August 1, 2020. We estimate that the study will need to continue for 3 years to reach the intended goal of 750 participants. A list of study centres can be obtained from the clinical trials registry website: https://clinicaltrials.gov/ct2/show/NCT04313335

### Eligibility criteria {10}

Patients presenting to the Department of Emergency, Dermatology, Neurology or Pain Management at any participating centre will be screened for eligibility to join the present study. Patients aged more than 50 years who are diagnosed with uncomplicated HZ, present with vesicles within 72 h of their emergence, and have an average pain score of at least 40/100 mm on a visual analogue scale (VAS, 0 = no pain, 100 = worst possible pain, at opposite ends of a 100-mm line) will be considered to fulfil the inclusion criteria. Patients who refuse to participate in the study or to provide written informed consent; those who have a raw score of more than 50 points on the Zung Self-Rating Depression Scale [26]; those who are confirmed to have HZ with head, neck, ocular, mucous membrane, cranial nerve, or central nervous system involvement or generalized HZ; those who are observed to have haemorrhagic or necrotizing lesions, satellite lesions, abnormal vesicles or acute retinal necrosis; those who have been on immunosuppressive therapy or mono- or multi-pharmacotherapy that involves any tricyclic antidepressant, valacyclovir, duloxetine or cytotoxic medications before acute HZ onset; those who have been diagnosed with hepatic, renal or immune dysfunction; those who are pregnant or breastfeeding; those with recorded hypersensitivity to the study drugs; those with contraindications to valacyclovir or duloxetine; and those who have been immunized with the HZ vaccination will be excluded from the study. Prior to the initiation of this study, research assistants (at least 2 research assistants per centre) will be trained regarding the details of this study protocol to ensure that the work would proceed smoothly. When patients are identified and diagnosed with acute HZ, research assistants will be informed and asked to screen the patients for eligibility. Eligible patients who are willing to participate will be recruited for the study.

